## Abstract

**Introduction:**

Functional training has been shown to be a viable alternative for the elderly and patients with chronic obstructive pulmonary disease (COPD). However, whether the combination of this type of training with aerobic and resistance training, commonly performed in pulmonary rehabilitation (PR) programs, induces more pronounced effects on daily physical activities and functionality remains unclear. The aims of the study will be to evaluate the short-term and sustained effects of the combination of a functional circuit program with a training program consisting of aerobic and resistance exercise.

**Methods:**

In this randomized controlled trial, patients with COPD will be randomly assigned (1:1:1) to an 8-week training program to follow one of the three *a priori* defined groups: (I) resistance and aerobic and functional exercises, (II) a conventional program including only resistance and aerobic exercises, or (III) a usual care program. Patients will be evaluated before and upon completion of 8 weeks of training regarding physical activity in daily life (PADL) using an activity monitor (accelerometer), activities of daily living (London Chest Activity of Daily Living), functional exercise capacity (6-minute walk test), and muscle strength (dynamometry). Additionally, the sustained effects of the interventions will be evaluated 22 weeks after commencing the study.

**Discussion:**

The inclusion of a protocol of functional physical training in the training conventionally performed by patients with COPD as an alternative to increase PADL and functionality may provide subsidies for the treatment of these patients, representing an advance and impacting on the physical training of patients with COPD.

**Trial registration:**

Brazilian Clinical Trials Registry (ReBEC) ID: RBR-3zmh3r. Registered: March 7, 2018.

## Introduction

Despite its primarily respiratory character, chronic obstructive pulmonary disease (COPD) also presents extrapulmonary consequences, including the reduction in functional exercise capacity and musculoskeletal function (i.e., strength and peripheral muscular resistance) [1, 2]. It is known that, to avoid the symptoms of the disease, these patients are less active when compared with healthy individuals of the same age group, presenting less time in physical activity, at a lower intensity and number of movements per day [3–8]. Lower levels of physical activity in daily life (PADL) are associated with a higher risk of hospitalizations and worse prognosis in COPD [9, 10], besides contributing to the progression of the disease [11].

As an attempt to counteract these consequences, pulmonary rehabilitation (PR) programs including physical training have been proposed as a key element in the treatment of COPD [12, 13]. Physical training is associated with an improvement in the functional exercise capacity and a reduction in dyspnea in these individuals [14, 15]. Resistance and aerobic training are among the exercises commonly proposed for these patients [12, 13, 16]. The combination of these modalities has been shown to be the best form of training for these individuals [17] as well as being recommended by international guidelines for the clinical treatment of these patients in PR programs [13, 18]. Despite the functional gains obtained in PR programs, the evidence for increased PADL in patients with COPD is still contradictory and inconsistent [19], especially in short-term PR programs [20–24].

Functional physical training has been shown to be an effective alternative for improving mobility, functionality, and performance in the activities of daily living (ADLs) of older adults [25–27]. This type of training includes muscle work involving coordinated patterns of multi-joint movements and dynamic tasks in order to improve functionality. Studies demonstrate positive functional effects of this type of exercise for patients with COPD [22, 28].

Sewell et al. [28] demonstrated improvement in PADL and ADL performance after a short-term training program combining functional exercises with aerobic and home training in patients with COPD. Despite the benefits obtained, the authors did not evaluate whether the responses were maintained for a longer period of time than the program period and did not include the progressive resistance training, an essential component for these patients. It is still unknown whether the addition of a functional circuit training (structured on the basis of the limitations during ADLs) to a conventional combined aerobic and resistance training program, commonly performed and well established in PR programs, can improve PADL, ADL performance, and functionality of patients with COPD in the short term. In addition, it is unknown whether possible functional and PADL gains obtained in this type of training are maintained during a 3-month follow-up.

This randomized clinical superiority trial aims to evaluate the effects of the addition of a circuit of functional physical training to an 8-week combined training (aerobic and resistance) on PADL, ADL performance, functional exercise capacity, and peripheral muscle strength of patients with COPD. In addition, the effects of the interventions will be re-evaluated 3 months after the training completion. It is hypothesized that the proposed functional training will lead to behavioral changes, influencing the improvement in the performance of ADLs and, consequently, PADL, accompanied by functional improvement in patients with COPD.

## Methods

### Study design

A randomized clinical trial with follow-up will be conducted at the Center for Studies and Care in Physical Therapy and Rehabilitation of the Universidade Estadual Paulista (FCT/UNESP) in Presidente Prudente, Brazil. The study protocol was developed following the Standard Protocol Items: Recommendations for Interventional Trials (SPIRIT) 2013 Checklist guidelines (Additional file 1) [29]. The trial was registered at www.ensaiosclinicos.gov.br (ID: RBR-3zmh3r). The study design is shown in Fig. 1.

**Fig. 1 Fig1:**
[figure not shown]
Experimental design of the study

Initially, participants will participate in an assessment process over 2 weeks on non-consecutive days. The first day of evaluation will consist of anamnesis, obtaining personal identification data and investigation of pre-existing comorbidities, and performing spirometry to confirm the diagnosis of COPD by means of a portable spirometer MIR-Spirobank version 3.6 (MIR - Medical International Research, Roma, Italy). The interpretation will be in accordance with the American Thoracic Society (ATS) and European Respiratory Society (ERS) [30], and values of normality will be relative to the Brazilian population [31]. Limitations of ADLs will be evaluated by the London Chest Activity of Daily Living (LCADL) scale [32, 33]. It should be emphasized that the questionnaire will be applied through an interview, always by the same evaluator, who will carry out prior training to avoid possible biases in the interpretation of questions and answers. On the second day, a functional capacity evaluation will be performed using the 6-minute walk test (6MWT). On the third day of evaluations, the measurement of peripheral muscle strength will be performed by means of a digital dynamometer. Patients will receive a physical activity monitor (accelerometer) which will be used during 7 days before the beginning of the training period, together with the basic guidelines for using the equipment. After the initial evaluation period, the training phase will begin. Conventional sessions will include resistance training and aerobic training. Resistance training plus functional circuit will include resistance training and performing a functional training circuit. Respiratory sessions will include only respiratory physiotherapy techniques.

After the end of the training period (8 weeks), all the evaluations described above, except for the spirometry, will be repeated. Finally, a follow-up will be performed 3 months after the end of the training period, evaluating the PADL, limitations in the performance of ADLs, functional exercise capacity, and muscle strength.

### Participants

For this study, 75 patients with COPD from the municipality of Presidente Prudente and the region will be recruited through telephone contact and the distribution of leaflets and medical referrals. The following inclusion criteria will be considered: (1) patients with COPD diagnosed according to the Global Initiative for Chronic Obstructive Lung Disease (GOLD) [34], (2) clinically stable patients without exacerbations or changes in medications for at least 30 days, (3) patients who do not use long-term oxygen therapy at home, (4) patients without pathological conditions that prevent the performance of physical activity, (5) absence of severe or unstable heart disease, and (6) do not participate in another structured exercise program. The study was approved by the research ethics committee of the FCT/UNESP in Presidente Prudente, Brazil (#77909317.2.0000.5402).

### Analysis of the population

Exclusion criteria are complications that prevent the continuity of the training protocol as well as low adhesion rate to the training protocol (below 75% of all sessions) [35]. In the event of two consecutive absences from training sessions, patients will be contacted by telephone to confirm the reason. An intention-to-treat analysis will be performed using the patient’s most recent assessment in case of withdrawals or absence of data. In case of possible injuries occurring during the intervention period, the individuals will be referred for appropriate treatment.

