## Procedures

### Interventions

The physical exercise program will take place over 8 weeks with a frequency of three weekly sessions of about 60 min each, totaling 24 training sessions. The sessions will begin with dynamic general stretching, after which the aerobic training will be carried out on a treadmill with a duration of 30 min, followed by the resistance training of upper limbs and lower limbs. These dynamics will occur for both the FTG and CTG, except for the third weekly session in which the FTG will perform functional training in circuit format. At the beginning, during, and at the end of the sessions, vital signs will be checked. The UCG will perform only usual care involving respiratory physiotherapy sessions that include inhalation therapy, pulmonary deflation techniques, diaphragmatic awareness, and inspiratory muscle exercise.

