### Sample size calculation

This is a superiority trial in which sample size determination was performed through prior study [45] information based on the primary PADL variable. With the expectation of an increase in the number of steps of 45% (approximately 2260 steps) in the FTG compared with the CTG and UTG (both with no expected increase), using a standard deviation of 2603 steps, and loss at follow-up of 20% of individuals (values commonly found in the study population) [44], 25 individuals will be required in each of the three groups to obtain a power of 80%, adopting an α of 5%.

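### Complications and attendance below 75% are exclusion criteria applied after randomisation, beside an intention-to-treat promise, and the plan does not say what these patients are excluded from

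*Protocol article*

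**What the plan says.** The six eligibility criteria are in the Participants section of the protocol article. The next section, Analysis of the population, adds a second set: "Exclusion criteria are complications that prevent the continuity of the training protocol as well as low adhesion rate to the training protocol", the limit being "below 75% of all sessions". After a sentence on telephoning patients who miss two sessions in a row, the paragraph continues: "An intention-to-treat analysis will be performed using the patient’s most recent assessment in case of withdrawals or absence of data".

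The Interventions section describes an exercise programme of three sessions a week for 8 weeks, "totaling 24 training sessions". For the third arm it says: "The UCG will perform only usual care involving respiratory physiotherapy sessions", and gives no number of sessions. The Methods paragraph of the Abstract, however, covers all three arms when it says that "patients with COPD will be randomly assigned (1:1:1) to an 8-week training program". The Study design section also lists respiratory sessions alongside the two kinds of exercise session in the training phase.

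Study design further says that the evaluations, apart from spirometry, are repeated after week 8, and that a follow-up takes place 3 months after training ends. It exempts nobody from either.

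**The concern.** An exclusion criterion normally acts before randomisation. These two cannot. Complications and poor attendance arise during treatment, and both can depend on the assigned programme and on how ill or motivated the patient is. If patients are dropped from the analysis on these grounds, the groups compared are no longer the groups that were randomised, and the analysis is not intention-to-treat whatever it is called.

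The rule decides who is in the primary analysis. As the paragraph stands, the team could apply either population after seeing the data and point to the protocol in support.

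**Working it through.** **1. When the criteria can be known.** The threshold is 0.75 × 24 = 18 sessions, so a patient with fewer than 18 fails it. Failure becomes certain at the seventh missed session (24 − 7 = 17). At three sessions a week, that is in week 3 at the earliest. Complications that interrupt training likewise occur only once training has begun. Neither criterion can be a screening criterion, and neither is in the Participants list.

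**2. What excluded could mean.** Three readings are possible.

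| Reading | Training | Later assessments | Analysis | Intention-to-treat? |
|---|---|---|---|---|
| A | stops, or patient classed as non-adherent | done | measured values, allocated group | yes |
| B | stops | not done | last value carried forward, allocated group | all patients counted, outcomes imputed |
| C | stops | not used | patient removed | no |

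The evidence points in different directions:
- The section heading and the term exclusion criteria point to C.
- The reference to continuity of training, and the carry-forward sentence, point to A or B.
- The repeat evaluations in Study design, with no exemption, point to A.
- The carry-forward sentence covers withdrawals and absent data. It does not mention patients excluded by rule who could still be measured.
- No per-protocol set is named to which the threshold might belong.

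None of the three readings is stated.

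**3. Which arms the rule covers.** The count of 24 belongs to the exercise programme, and UCG has no count of its own, which suggests that the rule covers only the two exercise arms. The Abstract and Study design place UCG in the 8-week programme with sessions of its own, and the threshold names no arm, which suggests all three. The question is open.

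**4. Effect on size.** The plan's own figure reproduces. With a difference of 2260 steps ("increase in the number of steps of 45% (approximately 2260 steps) in the FTG"), SD 2603, two-sided α of 5% (two-sided is an assumption) and 80% power:

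n = 2 × [2603 × (1.960 + 0.842) / 2260]² = 20.82, and 20.82 × 1.2 = 24.99, that is, 25 per group.

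By the normal approximation, power is 86.6% if all 25 per group are analysed, before any dilution from non-adherence, and 78.4% with 20 per group. The plan does not say whether its 20% loss allowance includes patients excluded under this rule, so the sample size section does not settle the reading.

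The documents give no non-adherence rate and no link between attendance and outcome, so the bias under reading C cannot be calculated. The following shows only how much it depends on unknowns. **Assumptions, none from the documents:** no true effect; the least adherent share q is removed from one arm of 25 and nobody from the other; attendance has correlation r with the outcome as analysed (a change in steps); the SD of that outcome is 2603.

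Spurious difference = r × φ(z_q)/(1 − q) × 2603, where φ is the standard normal density and z_q its q-quantile. Its standard error is 2603 × √[1/(25(1 − q)) + 1/25].

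| r | q | Spurious difference (steps) | Two-sided type I error |
|---|---|---|---|
| 0.2 | 10% | 102 | 5.2% |
| 0.3 | 20% | 273 | 6.4% |
| 0.5 | 30% | 646 | 12.5% |

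If both arms lose the same share with the same r, the difference is zero. If the comparator loses more at the same r, the sign reverses.

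**The case against.** The best defence is that nothing in the paragraph says these patients leave the analysis. The criteria are tied to continuing the training, intention-to-treat is promised explicitly, and the carry-forward rule gives withdrawn patients a value. On that view they stop training, count as withdrawals and remain in the analysis. This reading is coherent, so a reader who infers that the two statements can never both hold goes too far. But the text does not state it, and what stands is an unresolved conflict.

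Four stronger inferences are tempting, and the documents do not support them:
- **That the rule spares UCG**, so that sicker patients leave only the exercise arms. The Abstract and Study design leave open that UCG is covered too.
- **That the bias favours exercise.** No direction can be derived. In the contrast between functional circuit and conventional training, both arms face the same rule and share two of three weekly sessions.
- **That non-adherers who simply walk less would produce a spurious gain in steps.** A stable difference in level is present at baseline as well and would largely cancel in the planned pre, post and follow-up comparison. Bias requires non-adherers to differ in change.
- **That power falls because these exclusions come on top of the 20% loss in every arm.** Nothing says that the allowance omits them, and under the promised analysis all 25 per group remain.

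**Conclusion.** The concern holds as a conflict that the protocol must resolve. It names exclusion criteria that can be met only after randomisation, under a heading about the analysis population. It promises intention-to-treat in the same paragraph and does not say what the excluded patients are excluded from. This is a fault in what is written, not a detail that a condensed article leaves out.

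The consequence is conditional. If these patients leave the analysis, the result is not intention-to-treat and the comparison of arms is open to selection bias. If they leave assessment only, all are counted but obtainable outcomes are replaced by earlier ones, which for a patient not assessed after baseline means the baseline value. If they leave training only, no harm is done, but the text should say so. The illustrative figures rest wholly on assumed inputs and are not an estimate for this trial.

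**What to change.** Rewrite the opening of Analysis of the population to say that:
- complications and attendance below 75% do not remove a patient from the trial or from the primary analysis;
- all randomised patients are invited to the week-8 and 3-month assessments, whatever their attendance;
- all are analysed in their allocated group;
- the 75% threshold serves only to define a secondary analysis labelled per-protocol, with a statement of how it applies to UCG and against what number of sessions.

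Whether and when a patient stops training is a clinical matter that this change leaves alone.

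The cost is small. The visits are already scheduled, so the extra work is following up non-adherers at them. The effect estimate may be slightly smaller than one taken from adherent patients only.

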## Discussion

### Potential impact and significance of the study

The present proposal was developed through extensive literature research on this topic. Through the interpretation of the results found in several studies, it was possible to develop this concise and structured training protocol. The use of this protocol in the treatment of COPD will confirm whether the addition of functional physical training to a conventional training will promote positive effects on PADL and functionality and whether there will be maintenance of possible gains at the 3-month post-training follow-up.

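### Carrying the last assessment forward gives every lost patient zero change after week 8, so at the planned 20% loss the estimated decline to 3 months is only 80% of the true decline

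*Protocol article*

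**What the plan says.** The Analysis of the population section promises an intention-to-treat analysis that uses the patient's "most recent assessment in case of withdrawals or absence of data". This is last observation carried forward. It is stated as one rule for all outcomes and visits, and the article names no other method for missing data.

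There are three assessments: before training, at week 8 ("After the end of the training period (8 weeks), all the evaluations described above, except for the spirometry, will be repeated") and 3 months after training. The last one is a declared aim. The Abstract says that "the sustained effects of the interventions will be evaluated 22 weeks after commencing the study", and the section on potential impact says the trial will show "whether there will be maintenance of possible gains at the 3-month post-training follow-up".

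The Sample size calculation allows for "loss at follow-up of 20% of individuals". It does not say how much of that loss falls before or after week 8.

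**The concern.** The trial asks how much of a week-8 gain remains at 3 months. For each patient without a 3-month assessment, the rule supplies the answer instead of leaving it to be estimated. For someone lost after week 8 the whole gain counts as kept. For someone lost before week 8 no gain is recorded, and so no decline either. Every lost patient thus pulls the estimated decline towards zero.

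Two results are exposed: the maintenance result and, through early losses, the week-8 effect on the primary outcome. How far each moves depends on when patients leave and how fast the gain fades. Neither is known in advance, and the second is what the follow-up is meant to measure.

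**Working it through.** **Inputs, all from the Sample size calculation.** Effect: "With the expectation of an increase in the number of steps of 45% (approximately 2260 steps) in the FTG". Comparators: "both with no expected increase". Spread: "using a standard deviation of 2603 steps". Total loss: 20%.

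**The plan's own figure.** With two-sided alpha 5% (sidedness assumed) and power 80%, n per group = 2 × [2603 × (1.960 + 0.842) / 2260]² = 20.8. Multiplying by 1.2 gives 24.99, so the stated 25 per group is reproduced. Dividing by 0.8 would give 27. The sample size is not in dispute here.

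**Assumptions, since the article gives no values.** Let a be the share lost before week 8 and b the share lost after it, with a + b = 0.20. Let f be the fraction of the gain that has gone by follow-up. Loss is unrelated to outcome, and a lost patient does not return. The comparators have a mean change of zero, so carry-forward does not move their means.

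**Expected values under carry-forward**

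- Week-8 effect: (1 − a) × 2260.
- Follow-up effect: (1 − a − b) × 2260(1 − f) + b × 2260. The true value is 2260(1 − f).
- Bias at follow-up (second line minus truth): 2260 × [b·f − a(1 − f)].
- Decline from week 8 to follow-up (first line minus second): (1 − a − b) × 2260f = 0.80 × 2260f. The true value is 2260f.

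The last line does not depend on how a and b divide the 20%. If half the gain is lost, the true decline is 1130 steps and the estimate is 904. If all of it is lost, 2260 becomes 1808.

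**Bias in the follow-up difference (steps)**

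| Loss before / after week 8 | Week-8 effect | f = 0 | f = 0.5 | f = 1 |
|---|---|---|---|---|
| 0% / 20% | 2260 | 0 | +226 | +452 |
| 10% / 10% | 2034 | −226 | 0 | +226 |
| 20% / 0% | 1808 | −452 | −226 | 0 |

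**Apparent retention (follow-up effect divided by week-8 effect).** When true retention is 75%, 50% and 0%:

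- All loss late: 80%, 60% and 20%.
- 10%/10% split: 77.8%, 55.6% and 11.1%.
- All loss early: 75%, 50% and 0%. The ratio is then right, because the week-8 effect and the decline shrink by the same factor.

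**Simulation check.** This used 25 per group, SD 2603 and random loss. The correlation between visits is assumed, at 0.6 here.

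- All loss late, f = 1 (true difference 0): carry-forward gives about 463 steps, observed data 13.
- All loss late, f = 0.5 (true difference 1130): carry-forward gives 1360, observed data 1139.

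**False-positive rate at follow-up.** With all loss late and f = 1, correlation 0.5 to 0.7:

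- Baseline-adjusted two-arm test: roughly 9 to 13% across runs, against a nominal 5%.
- Unadjusted two-arm test: about 8 to 10%.
- Three-group Tukey criterion on change from baseline, as an approximation to the planned analysis: about 4 to 6% for the FTG–CTG pair, against roughly 2% without missing data.

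At about a 10%/10% split the baseline-adjusted rate is 6 to 7%. With all loss early it stays near 5%.

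**The case against.** The strongest reply is that the harm depends on circumstances the article does not establish. Most of that stands.

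- A reader might infer that the rule credits everyone lost before follow-up with a fully kept gain. It does not. Patients lost before week 8 carry baseline and are credited with no gain.
- A reader might infer that the rule always favours a sustained benefit. The table shows overstatement, no bias and understatement, all at the same 20% loss. Only the decline in steps has a fixed direction.
- A reader might take an error rate of 11 to 13% as a property of this trial. It needs all loss late, complete decay and a baseline-adjusted two-arm test. The Statistical analysis section plans a two-way ANOVA with Tukey comparisons, where the inflation is from about 2% to about 4 to 6% for that pair.
- The largest follow-up overstatement and the full 20% dilution at week 8 cannot both occur, since each needs all the loss on a different side of week 8.
- At week 8, carry-forward with random loss shrinks the effect and cannot create a false benefit.
- The simulations used random loss, so they do not show that another analysis is unbiased if patients leave because they worsen. The article gives no reasons for dropout.

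What does not stand is a defence of the rule as cautious, or as a detail left to a fuller plan. The article states the rule itself, and its caution or optimism depends on timing and decay that nobody knows beforehand.

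**Conclusion.** The point holds in a conditional form. Under the stated rule and the plan's own 20% loss, if unrelated to outcome, the estimated decline from week 8 to 3 months is 80% of the true decline in steps, however the loss is timed. This bears directly on the maintenance question.

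The follow-up difference may be wrong by anything from about +450 to about −450 steps on a planned effect of 2260, and is unbiased in some settings. The week-8 effect lies between 2260 and 1808. These figures rest on assumed timing, decay, loss without return and unchanged comparators. The error rates also rest on an assumed correlation. The documents do not support a claim of one-directional bias or of a doubled error rate in the planned test.

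**What to change.** In Analysis of the population, replace the carry-forward sentence. Suggested text: the main analysis will use a likelihood-based mixed model for repeated measures on all observed visits of all randomised patients, with group, visit and their interaction, taking baseline into account, and without single imputation; last observation carried forward will be reported as a supplementary analysis only.

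The Statistical analysis section then needs matching wording, including how the pairwise group comparisons are adjusted within the model.

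The model is valid when loss is random given the observed data, and the text should say so. A sensitivity analysis that assumes worse outcomes after dropout would be a useful but optional addition.

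The cost is small: a few sentences, a different procedure in the SPSS package already named, and slightly more analysis work. The visits, data collection and sample size stay as they are.
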